### Participant and Public Involvement Statement

Community members will be involved from the beginning of this study, including during the development of research questions, outcome measures, and study design. As previously described, this study will be co-developed with input from local partners including the Auburn Rural Studio and the Black Belt Community Foundation and is guided by a community advisory committee composed of local residents and community leaders. The local partners and community advisory committee provided feedback on the survey content and overall study approach to ensure alignment with community priorities. The advisory committee reviewed study materials to assess the burden of participation and helped make sure the study design was respectful of all participants’ time and privacy. Community partners have also supported recruitment efforts by mailing flyers and organizing local outreach events. Community partners and leaders will be actively involved in the dissemination of results, including input on decisions on what findings to share, in what format, and when.

## Objective 1:

Measure the density of fecal microbes released to the local environment (enteric pathogens and fecal indicators) at the household and community levels before and after the implementation of a community-wide sanitation system.

### Overview of the Study Design

We are collecting longitudinal microbial density data from environmental and household samples to estimate the reduction of pathogens and fecal markers released into the environment following the expansion of the wastewater treatment intervention. From the 50 recruited households, we will collect soil, wastewater, and drinking water samples to analyze for fecal indicators and enteric pathogens. We will conduct longitudinal surface water sampling from the receiving waters upstream and downstream of the discharge point of the new wastewater treatment system. All community members—both participants and non-participants—will be made aware that community-level sampling will be taking place for the purposes of this study at the community meetings described previously.

We will culture fecal indicator bacteria (total coliforms and *E. coli*) from environmental and household samples (wastewater, soil, drinking water, and surface water) using the IDEXX Colilert-18 Quanti-Tray 2000 System as independent predictors of exposure risk, to develop pathogen:indicator ratios for use in risk modeling, and as proxy indicators of pathogen viability in samples. We will further analyze the soil, wastewater, and surface water samples for pre-specified pathogens and fecal markers by real-time quantitative PCR (qPCR) using a custom TaqMan Array Card (28). Targets are specified in Appendix 1. We will use the microbial data collected before and after connection to the intervention to inform an interrupted time series (ITS) analysis. We are particularly interested in assessing the impact of the intervention on pathogens in the environment through drinking water, surface water, and soil sampling as proximal, objective, quantitative measures on the causal pathway from the intervention to all downstream health and non-health effects of improved sanitation services.

### Drinking Water Sample Collection

We will collect drinking water samples from all 50 households at each of the six time points. All of the households will have a 1000 mL and 50 mL grab sample of their drinking water collected. This grab sample will be used for analysis as outlined above.

### Soil Sample Collection

At each of the six time points, three soil samples will be collected from an area thought to be impacted by failing sanitation, as identified by the participant living in the household. If the household is relying on a cesspool or straight pipe, a sample will be collected directly at the point of impact by collecting the top layer of the receiving soil, with additional samples collected one foot away and three feet away from the point of impact. If the household is relying on a septic tank with a septic field, soil samples will be collected from three randomly selected locations overlaying the septic field. Impacted soil samples will not be collected at the 10 households with existing adequate sanitation services, which, by definition, have no directly impacted soils. As a control, three additional soil samples will be collected at all 50 households during each of the six sampling time points in a section of the yard that is identified by the participant as unimpacted by failing sanitation. If no such area exists, then the researcher will randomly sample at three locations at the front, side, and back of the home. Once initially selected, the same household soil locations will be sampled at each of the six time points.

### Wastewater Sample Collection

At each of the six time points, one wastewater sample will be collected at the household’s wastewater receiving site. The sample collected will depend on the participant’s current sanitation infrastructure status. For example, wastewater samples from households that utilize a septic tank will be collected directly from the tank. For households that utilize straight pipes or cesspools, a mixture of surface water, gray water, and human waste will be collected from the discharge site. Sampling directly from the pipe itself will not be possible because flow only occurs during use, such as flushing the toilet, which would be difficult to time and any sample obtained may reflect waste from one individual at one time point. Sampling from the receiving environment will provide a more representative sample of waste discharges and environmental impact. Households that are connected to the municipal wastewater treatment system will not have wastewater samples collected at the household; instead, researchers will collect wastewater influent from the municipal system three randomly selected times during the bounds of each time point. These samples will allow for estimation of pathogen loading to the environment under various containment or discharge scenarios.

### Sample Collection from Receiving Stream

Surface water samples will be collected from two creeks at publicly accessible points upstream and downstream of the town serviced by the intervention and at the future effluent discharge point. These samples will be collected during each environmental sampling time point, which refers to a defined sampling period during which all enrolled households are sampled. After each household is connected to the intervention, 15 samples per time point will be taken of the treatment system influent, 15 samples per time point will be taken at the treatment system effluent prior to UV disinfection, and 15 samples per time point will be taken at the treatment system effluent after UV disinfection.

### Data Analysis and Outcomes

Our primary outcome is to compare the concentration of culturable *E. coli* in the environment pre- and post-intervention using a time series regression analysis suitable for an interrupted time series ITS design. We will use the Durbin-Watson statistic to test the presence of autocorrelation in *E. coli* concentrations over time and will adjust for autocorrelation if found (29). To determine regression estimates that express the level (the average value of *E. coli* concentration at a given time point) and trend (the direction and rate of change in *E. coli* concentrations over time) of the outcomes pre- and post-intervention, we will use the generalized least-squares method with the Prais-Winston estimator (29). Regression coefficients corresponding to standard effect sizes on culturable *E. coli* soil concentrations will be obtained for a step change and a change in trend pre- and post-intervention. A step change, also known as a change in level, is the difference between the observed level at the first intervention time point and the predicted time trend. A change in trend is defined as the difference between the post-intervention and pre-intervention slopes, where slopes are defined as the rate of change in *E. coli* concentration over time (30).

Our secondary outcomes are the estimated prevalence of individual pre-specified pathogens in soil, wastewater, and surface water samples. We will graph the mean and standard deviation scores (the average measured values) for fecal markers and composite measurement, which summarizes the presence or concentration of multiple enteric pathogens within a sample. Within each sample type, only markers and composite indicators appearing in at least 10% of the samples collected at each time point will be included, in order to visualize the trends in fecal indicator concentrations and pathogen prevalence.

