## Methods and analysis:

We will collect repeated environmental and household samples (wastewater, soil, drinking water, and surface water) across six structured time points to evaluate changes before and after intervention implementation, as outlined in Figure 1. All samples will be cultured for *E. coli*, and all soil, surface water, and wastewater samples will be analyzed for pre-specified enteric pathogens and fecal markers using quantitative PCR (qPCR). In addition to environmental sampling, structured surveys are conducted at selected time points: a demographic survey at time point one, sanitary inspection surveys at time points two and five, and a well-being survey at time points three and six (Figure 1). Further detail on survey content and analysis is provided in the detailed objectives below. The study began in August 2024 and will conclude at least three months after the final household in Phase II is connected to the intervention, currently targeted for December 2026. Each household follows the same six-point sampling schedule, although the exact dates vary depending on when the intervention reaches each home.

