### Sample Size Calculations

We calculated a sample size for our primary outcome using a time series regression appropriate for an ITS design. Here we calculate the number of households, *n*, that will be followed longitudinally across the six sampling time points, *t*, (three before and three after the intervention) to detect a meaningful change in soil *E. coli* concentrations with 80% power at a 5% significance level. Equation 1 calculates the crude number of households, *m*, needed before accounting for clustering (27).

Equation 1
$$m=\frac{2{\left(z_{\alpha }+z_{Q}\right)}^{2}\sigma^{2}\left(1-\rho_{1}\right)}{ts_{x}^{2}d^{2}}$$

In this equation the term *σ*^*2*^ captures the total variability in *E. coli* concentrations across all locations and time points, while *s*
^*2*^ accounts for the variability in repeated measurements within the same location. The intraclass correlation coefficient, ρ_1_ reflects how similar those repeated measures are over time for a given household. Finally, the effect size, *d*, is the expected change in log-transformed *E. coli* concentrations in soil attributable to the sanitation intervention.

To estimate the values used in this calculation, we used log-transformed concentrations of *E. coli* ybbW in soil samples based on preliminary data from soil samples collected in Hale County in 2023 (22). For sample size calculations, we assumed that *E. coli* ybbW in soil could serve as a proxy for culturable *E. coli* in soil, based on a moderate positive correlation observed between the two measures in soil samples (Spearman’s ρ = 0.54, *p* = 0.03). The total variance, *σ*^*2*^, was calculated as 5.2 log (copies/gram)^2^ based on all available soil samples. The within-household variance, *s*
^*2*^, was estimated as 4.3 log (copies/gram)^2^ from a mixed-effects model including a random intercept for location. The intraclass correlation coefficient, *ρ*_1_, which reflects the correlation of repeated measurements within a single location over time, was estimated to be 0.16. The effect size, *d*, was defined as a 0.45-log (copies/gram) reduction in soil concentrations, which corresponds to 20% of the standard deviation of log-transformed values from the pilot data. We selected this threshold to reflect a small but meaningful reduction in environmental fecal contamination. Using these inputs and *t* = 6 time points per household, we calculated an intermediate value of *m* = 13 households needed before adjusting for clustering.

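### Fitted to six time-point means or to one household's six visits, the named Durbin-Watson and Prais-Winsten steps fail, and the plan does not state the unit of analysis

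*Protocol article*

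**What the plan says.** The Data Analysis and Outcomes section under Objective 1 sets out the primary analysis in sequence. First comes a test: "We will use the Durbin-Watson statistic to test the presence of autocorrelation", with an adjustment to follow if any is found. The next sentence names the estimator for level and trend without repeating that condition: "we will use the generalized least-squares method with the Prais-Winston estimator" (the estimator is Prais-Winsten). Coefficients are then to be obtained "for a step change and a change in trend pre- and post-intervention". Level is defined as "the average value of *E. coli* concentration at a given time point", and no household, replicate-sample or calendar-round term is mentioned.

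Sample Size Calculations fixes six time points, "three before and three after the intervention". The opening of Methods and analysis adds: "Each household follows the same six-point sampling schedule, although the exact dates vary". The sample-size section calls its method a time series regression too, but it sizes the study as about 30 households followed over time. It uses a within-household correlation of 0.16 and a clustering correlation of 0.17 for three soil samples per visit.

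**The concern.** Durbin-Watson and Prais-Winsten are tools for one long, equally spaced series. The definition of level as an average at a time point, with no household term, most naturally describes a series of six means. A four-parameter model on six points leaves two residual degrees of freedom. The pattern of the residuals is then set almost wholly by the design, so it says nothing about real autocorrelation. A correction estimated from those residuals treats neighbouring errors as offsetting each other and makes standard errors too small. The p-value and confidence interval of the primary outcome are at stake: a sanitation effect could be declared from noise.

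**Working it through.** **1. The plan's own figure.** Inputs from Sample Size Calculations: total variance 5.2, within-household variance 4.3, correlation 0.16, effect 0.45 log, t = 6, 80% power, 5% significance (taken as two-sided).

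Equation 1: m = 2 × (1.960 + 0.842)² × 5.2 × (1 − 0.16) / (6 × 4.3 × 0.45²) = 13.12, stated as 13.

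Equation 2 as printed: 13 × (1 + 0.17) × (3 − 1) = 30.4, stated as about 30.

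Both figures reproduce; this does not endorse the formulas. The relevance is that the sizing counts households with correlated repeated samples, not six points.

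**2. Residual degrees of freedom on a six-point series.** Intercept, slope, step and change in slope are 4 parameters; 6 − 4 = 2.

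**3. Durbin-Watson.** A line through three equally spaced points leaves residuals proportional to (1, −2, 1). The six residuals are therefore (a, −2a, a, b, −2b, b).

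- Sum of squares: 6a² + 6b².
- Sum of squared successive differences: 18a² + 18b² + (b − a)².
- DW = 3 + (a − b)² / [6(a² + b²)]. The minimum is 3.00 (a = b) and the maximum 3.33 (a = −b).
- Lag-1 residual correlation = −2/3 + ab / [6(a² + b²)], always between −0.750 and −0.583.

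This is algebra and assumes no error model. Equal spacing is needed for the exact bounds; in the unequal spacings tried, DW stayed within 2.85-3.33.

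**4. Information in the test.** For true autocorrelation from −0.3 to 0.8, mean DW was 3.16-3.18. An exact 5% test rejected 4.5-5.7% of the time, so it has no power.

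**5. False positives on a six-point series.** Simulated with no effect, nominal 5%, t with 2 degrees of freedom:

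| True errors | Method | Step | Trend change |
|---|---|---|---|
| Independent | Ordinary least squares | 4.9% | 5.1% |
| Independent | Prais-Winsten, one-step | 13-19% | 17-24% |
| Independent | Prais-Winsten, iterated | 20-31% | 25-37% |
| Autocorrelation 0.5 | Ordinary least squares | 6.4% | 9.4% |
| Autocorrelation 0.5 | Prais-Winsten, across variants | 21-35% | 32-48% |

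The ranges reflect how the autocorrelation is estimated. The Prais-Winsten rows apply the correction to every series.

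**6. Stacked household data (30 × 6), no shared shocks.** The lock disappears. For true autocorrelation from 0.5 down to 0, median DW is 0.7-1.4 without household effects in the model and 1.4-2.0 with them. Prais-Winsten type I error is 3.2-4.8% and 3.3-8.0% respectively. Household-clustered standard errors give 4.4-5.6%.

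**7. Stacked data with a shock shared by all households in a round.** The documents give no size for such a shock. An SD of 0.2-0.3 log is assumed; the total SD is √5.2 = 2.28 log. Type I error for the step is 12-22% if all households are fully aligned in time, and about 5% if connection is staggered over five rounds.

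**The case against.** Four points can be made for the plan.

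- **The six-mean reading is not stated.** Sample Size Calculations describes about 30 households followed longitudinally. A reader might infer from step 3 that the analysis cannot work at all. The documents do not support that, because they leave the stacked reading open and there the lock is gone. This stands, and the finding is conditional for that reason.
- **The test need not always trigger the adjustment.** A reader might infer that a value near 3 always counts as autocorrelation found. That is so only if DW is compared with 2. An exact test fires about 5% of the time. Least squares unless that test rejects gave 5.0-8.6% for the step and 5.3-8.8% for the trend change. This stands too. The large inflation requires Prais-Winsten to be applied regardless, as the sentence naming it reads, or a comparison with 2. The article does not settle which is meant.
- **The shared-shock figures rest on an assumption.** Connection is staggered, 20 comparison households are planned, and Limitations promises rainfall monitoring and adjustment through comparison sites. This stands: 12-22% is not an estimate for this design. However, the regression as described contains no such term. The degree of alignment is also unclear: the receiving-stream section treats a time point as one period covering all households, while the opening of Methods lets dates differ.
- **Random effects and degrees of freedom may sit in an analysis plan not shown.** True, and their absence alone would be no finding. But the article itself fixes the test, the estimator and the coefficients, and it is those choices that fail on a 3 + 3 series.

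**Conclusion.** The concern holds in conditional form. If the model is fitted to six time-point means, or to each household's six equally spaced visits, Durbin-Watson carries no information. Applying Prais-Winsten then raises the false-positive rate from about 5% to about 13-31% for the step and 17-37% for the trend change. Those rates assume independent errors, no true effect and a t test with 2 degrees of freedom. The DW range rests only on equal spacing.

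If the model is fitted to stacked household data, type I error is roughly 3-8% without shared shocks. What then remains is that the stated regression has no place for the household and replicate correlation on which the sample size depends. It is also exposed to shared shocks of unknown size to the extent that visits are aligned. The article does not say which reading applies, and its definition of level favours the first. The matter should be settled before post-connection results are analysed.

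**What to change.** State that the unit of analysis is the household soil sample. Replace the Durbin-Watson and Prais-Winsten steps with a linear mixed model on sample-level log10 culturable *E. coli*, with:

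- random effects for household, sampling spot and household-visit;
- calendar round or date;
- a time-varying connection indicator for the step;
- time since connection, so that the trend change remains an estimand;
- the comparison households. The 10 with adequate sanitation supply only unimpacted soil, so a soil-type term is needed if they enter the same model.

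Use small-sample degrees of freedom, or inference clustered or bootstrapped by household. The cost is analysis wording and some programming; no further sampling is required.

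### The 80% power is claimed for one 0.45-log change, but the analysis specifies a step change and a trend change; 30 connecting households give the step about 17–21% power

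*Protocol article*

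**What the plan says.** Sample Size Calculations plans six visits per household, "three before and three after the intervention", and sizes the study "with 80% power at a 5% significance level" for one effect, d, a reduction of 0.45 log. It describes the calculation as suited to an interrupted time series. Equation 1 gives 13 households and Equation 2 raises this to about 30.

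Data Analysis and Outcomes (Objective 1) names the pre/post comparison of culturable E. coli as the primary outcome. The estimates it then specifies are regression coefficients on soil E. coli that "will be obtained for a step change and a change in trend pre- and post-intervention". The step "is the difference between the observed level at the first intervention time point and the predicted time trend". The trend change is the post-intervention slope minus the pre-intervention slope. Estimation is by generalised least squares with an adjustment for autocorrelation if it is found. No average pre/post difference is named as an estimate, and neither coefficient is given its own effect size or power.

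**The concern.** The quantity that was powered and the quantities that will be estimated are different. A step measured against an extrapolated trend is much noisier than a difference of averages when the trend rests on three visits. If the 80% is read as applying to the step, a null step will be taken as evidence against a 0.45-log effect, although a true step of that size would be missed about four times in five. The trend change has no stated target at all, so its power cannot be judged from the document.

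**Working it through.** **Inputs.** All are from Sample Size Calculations unless noted.
- Total variance: "was calculated as 5.2 log (copies/gram)^2^ based on all available soil samples".
- Within-household variance: "was estimated as 4.3 log (copies/gram)^2^ from a mixed-effects model including a random intercept for location".
- Correlation of repeated measures: "was estimated to be 0.16".
- d = 0.45; t = 6; k = 3 samples; ρ₂ = 0.17.
- Connecting households: 50 enrolled (Objective 1 overview) minus 20 comparison households (Interrupted Time Series) = 30.

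**1. The plan's own figure.** With a two-sided 5% level, Equation 1 gives m = 2(1.96 + 0.842)² × 5.2 × 0.84 / (6 × 4.3 × 0.45²) = 13.1. Equation 2 as printed gives 13 × 1.17 × 2 = 30.4. Both stated figures reproduce. A one-sided level gives 10.3 and does not match.

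**2. Variance factors per household.** Take visits 1 to 6, a household intercept and independent visit errors with variance v.
- Step at visit 4: pre-trend extrapolated to visit 4, 1/3 + 2²/2 = 2.333; post line at visit 4, 1/3 + 1/2 = 0.833. Sum 19/6 = 3.167.
- Slope change: 1/2 + 1/2 = 1.0.
- Post mean minus pre mean: 1/3 + 1/3 = 0.667.
- Step against mean difference: 3.167 / 0.667 = 4.75.

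**3. Variance of a visit mean of three samples.** v = 4.3/3 = 1.433 if the samples are independent; v = 4.3 × (1 + 2 × 0.17)/3 = 1.921 if they correlate 0.17.

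**4. Power with 30 connecting households alone.** SE = √(factor × v/30); power = Φ(0.45/SE − 1.96) + Φ(−0.45/SE − 1.96).

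| Estimate | SE | Power for 0.45 log |
|---|---|---|
| Step | 0.389–0.450 | 21–17% |
| Mean difference, no control for secular change | 0.178–0.207 | 71–59% |

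The step detectable with 80% power is 2.80 × SE = 1.09–1.26 log. Households needed for 80% power on the step: (1.96 + 0.842)² × 3.167 × v / 0.45² = 176–236, against about 140 connections on offer (Description of Intervention).

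**5. Variants for the step.**
- One value per visit: about 10%.
- Total variance 5.2 in place of 4.3: 15–18%.
- AR(1) of 0.16 to 0.5: 18–34%.
- c comparison households sharing one linear trend: variance v[(7/6)/30 + 4/(60 + 17.5c)]. For c = 10, SE 0.283–0.328 and power 36–28%; for c = 20, SE 0.264–0.306 and power 40–31%.

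**6. Trend change.** The document states no target. At an assumed 0.15 log per visit, power is 9–10%; at an assumed 0.45 log per visit, 43–54%.

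**7. The average difference with secular change removed.** With free visit effects and all households crossing over together, variance = 0.667 × v × (1/30 + 1/c).
- c = 10: SE 0.357–0.413, power 24–19%.
- c = 20: SE 0.282–0.327, power 36–28%.

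The step handled in the same way takes 3.167 in place of 0.667. With c = 10 its SE is 0.778–0.901 and its power 9–8%, so the ratio of 4.75 is unchanged. If crossover is staggered, with an assumed ten households connecting at each of the third, fourth and fifth of six periods, the average has 28–36% power with c = 10 and 34–43% with c = 20.

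Soil Sample Collection excludes impacted soil at the 10 adequately served households. Only the 10 poor-sanitation households therefore give a like-for-like control.

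**The case against.** The strongest reply is that the average difference looks good only because it is quoted without control for secular change. This stands. The 59–71% belongs to an uncontrolled pre/post contrast, and the comparison-adjusted average falls to about 19–36% under simultaneous crossover. A reader might infer that renaming the primary parameter rescues the study's power; the figures do not support that. The size of the advantage also depends on the model. It is 4.75 in variance for the mean difference without a trend term, or when both estimates are contrasted with comparison households through free visit effects. It nearly vanishes if both assume one linear trend shared with 10 comparison households: the average then has variance v[0.667/30 + 9/(120 + 175)], SE 0.275–0.318, against 0.283–0.328 for the step.

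It is also fair to say that 17–21% leaves out the comparison sites and the autocorrelation adjustment, both of which the protocol intends to use. The variants above include them one at a time, and none comes near 80%.

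Two further inferences should not be drawn. One is that two coefficients tested at 5% give about 10% familywise error: the protocol states no rule that either one alone counts as success. The other is that the step is biased because soil still holds earlier contamination at the first post-connection visit: the document gives neither a persistence figure nor the interval from connection to that visit.

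Leaving the matter to an analysis plan does not answer it, because the protocol itself defines both coefficients and itself states the power.

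**Conclusion.** The power statement does not apply to the coefficients that the protocol specifies. For a 0.45-log step, power is about 17–21% from the connecting households alone and about 28–40% if 10 to 20 comparison households share a linear trend. Across all variants tried the range is about 10–40%. For the trend change no power is stated, and none can be derived without an assumed effect. The 17–21% rests on 30 connecting households, three samples averaged per visit with correlation 0 to 0.17, equally spaced visits, a household intercept, no autocorrelation, no dropout and the full 0.45 log appearing as the step. It also takes the gene-copy pilot variance as valid for culturable E. coli, as the protocol does.

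The uncontrolled mean difference also misses 80% (59–71%). That has a separate cause in the sample-size formula, and changing the parameter will not repair it.

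**What to change.** Before post-connection data are analysed:

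1. Name one primary parameter: the average within-household difference in log culturable E. coli in soil between connected and unconnected visits. State how secular change will be removed and which comparison households supply the control.
2. Report the step at the first post-connection visit and the slope change as secondary.
3. Replace the 80% statement with the power of the primary parameter under the model that will be used: about 59–71% if uncontrolled; about 19–24% with the 10 poor-sanitation comparisons, or 28–36% with 20, under free visit effects and simultaneous crossover. Recompute it for the expected connection schedule.

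This needs no extra samples, but it has three costs. The stated power becomes less favourable. The primary result no longer separates an immediate from a gradual effect. The comparison-adjusted estimate relies on parallel trends with a few non-randomised households, in place of adjustment for the connecting households' own pre-trend, which was a reason for choosing this design.
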